# PALLiON – PALLiative care Integrated in ONcology: study protocol for a Norwegian national cluster-randomized control trial with a complex intervention of early integration of palliative care

**DOI:** 10.1186/s13063-020-4224-4

**Published:** 2020-04-02

**Keywords:** Advanced cancer, Cluster-randomized trial, Palliative care, Integration, Patient-reported outcomes, End-of-life care

## Abstract

**Background:**

Several publications have addressed the need for a systematic integration of oncological care focused on the tumor and palliative care (PC) focused on the patient with cancer. The exponential increase in anticancer treatments and the high number of patients living longer with advanced disease have accentuated this. Internationally, there is now a persuasive argument that introducing PC early during anticancer treatment in patients with advanced disease has beneficial effects on symptoms, psychological distress, and survival.

**Methods:**

This is a national cluster-randomized trial (C-RCT) in 12 Norwegian hospitals. The trial investigates effects of early, systematic integration of oncology and specialized PC in patients with advanced cancer in six intervention hospitals compared with conventional care in six. Hospitals are stratified on the size of local catchment areas before randomization. In the intervention hospitals, a three-part complex intervention will be implemented. The backbone of the intervention is the development and implementation of patient-centered care pathways that contain early, compulsory referral to PC and regular and systematic registrations of symptoms. An educational program must be completed before patient inclusion. A total of 680 patients with advanced cancer and one caregiver per patient are included when patients come for start of last line of chemotherapy, defined according to national treatment guidelines. Data registration, clinical variables, and patient- and caregiver-reported outcomes take place every 2 months for 1 year or until death. The primary outcome is use of chemotherapy in the last 3 months of life by comparing the proportion of patients who receive this in the intervention and control groups. Primary outcome is use of chemotherapy in the last 3 months before death, i.e. number of patients. Secondary outcomes are initiation, discontinuation and number of cycles, last 3 months of life, administration of other medical interventions in the last month of life, symptom burden, quality of life (QoL), satisfaction with information and follow-up, and caregiver health, QoL, and satisfaction with care.

**Discussion:**

Results from this C-RCT will be used to raise the awareness about the positive outcomes of early provision of specialized palliative care using pathways for patients with advanced cancer receiving medical anticancer treatment. The long-term clinical objective is to integrate these patient-centered pathways in Norwegian cancer care. The specific focus on the patient and family and the organization of a predictable care trajectory is consistent with current Norwegian strategies for cancer care.

**Trial registration:**

ClinicalTrials.gov, NCT03088202. Registered on 23 March 2017.

## Background

Major concerns in oncology today are the rapidly increasing complexity of treatment, the steadily augmenting number of treatment lines that are administered, and new agents that increases the demand for anticancer treatment at end-of-life (EoL). Coupled with this is the increasing use of advanced imaging, i.e. computed tomography (CT) and positron emission tomography (PET) scans and magnetic resonance imaging (MRI). About one-third of the cost of cancer care is spent during the patient’s last year of life [1], and costs are expected to escalate rapidly, which threatens the sustainability of the present services [2, 3].

One article examined the rationale for discontinuation of chemotherapy for metastatic non-small-cell lung cancer (NSCLC) and identified a huge variability in these processes, unrelated to time of death [4], as addressed by others [5–7]. This is in spite of patients, families, and oncologists uniformly recognizing the administration of chemotherapy near death as aggressive and as an indicator of poor EoL care [8].

The American Society of Oncology (ASCO) has defined discontinuation of chemotherapy given with a life-prolonging intent in the last 2 weeks of life as a benchmark for improving clinical practice [9]. It is difficult to decide the optimal chemotherapy intensity during the last periods of life at an individual patient level. For example, if the treatment of choice in some patients with chemosensitive solid tumors is a therapy with modest side effects, a high response rate, and good symptom relief, this may be appropriate even if the life expectancy is < 3 months. However, a French registry-based study in > 279,000 patients found no clear pattern between the expected chemosensitivity of different solid cancers and the administration of chemotherapy at EoL [6].

Identifying the appropriate time to stop chemotherapy is challenging, but for the majority of patients chemotherapy should not be given during the last month of life [10, 11]. Generally speaking, it is rare that patients will benefit from chemotherapy in this phase, in fact it may even hasten death [12]. However, the physicians’ attitude and perceptions about oncological treatment, patients’ determination to continue treatment at whatever cost, or the reverse, that the patients’ wishes to spend more time at home and refrain from treatment, are not systematically taken into account in the decision-making process. Another challenging factor is that the patient may not be aware of the prognosis related to the actual diagnosis and stage, either because the prognostic conversation never took place, there was no treatment plan presented that delineated the different scenarios that may occur during the disease trajectory, or because information was provided, but not understood [13–15]. Taken together, these factors may contribute to overuse of anticancer treatment at EoL.

Patients with incurable disease treated with intensive anticancer treatment at EoL more often receive cardiopulmonary resuscitation, mechanical ventilation, or die in an intensive care unit [16]. Further, a study by Prigerson et al. in 2015 showed that use of chemotherapy was not associated with better quality of life (QoL) near death compared with non-use [12]. Interestingly, this was most pronounced in patients with a relatively good level of functioning. This contrasts results showing that a palliative care (PC) approach at an early stage in patients with unfavorable prognosis may improve patients’ QoL and symptom control, may lead to prolonged survival, and give patients and caregivers a more realistic perspective on the disease and prognosis [17–22]. Further, there is documentation that caregivers of patients with advanced cancer are generally more satisfied and report less depressive symptoms with an early introduction of PC [23], although findings are not entirely conclusive across studies.

These and related findings in the wake of the Temel study [24] initiated the current debate and have made international stakeholders advocate a stronger integration of oncology and PC for patients with incurable cancer [8, 25–27]. Despite a rapid development of PC services during the last 15–20 years, there is still a distinct separation between oncology and PC in Norway as in other Western countries. This infers that the potential for optimal care during the last phase of life for patients with advanced cancer has not been fully explored, despite the documented advantages.

Information given to cancer patients and caregivers about the disease and its treatment is important at all stages of disease and is crucial in relation to PC in order to facilitate shared decision-making, and improve satisfaction with care, patients’ sense of control, QoL, and communication between healthcare providers and patients and caregivers. As PC also aims to improve the QoL of caregivers [28], waiting to include caregivers until patients are in their last weeks or days of life may not adequately address patient or caregiver distress [13, 29]. However, results from studies on integration of oncology and PC from other countries such as the UK and United States, may not be directly transferable to Norway, given the different organization of healthcare, reimbursement issues, and indications for hospice use. Further, no national trials have been conducted yet.

On this background, we launched the PALLION study, a cluster-randomized controlled trial (C-RCT) in 12 Norwegian hospitals. The long-term objective is to improve the quality and efficacy of cancer care for patients with advanced cancer who receive chemotherapy. This will be achieved by means of a complex intervention consisting of the development and implementation of specific patient-centered care pathways (PCCPs) that delineate the treatment and care trajectory, make early referral to PC compulsory alongside anticancer treatment, and contain systematic registration of patient- and caregiver-reported outcomes (PROs) during treatment and follow-up. A prerequisite to succeed with the integration of oncology and PC is the specifically developed educational program for physicians to be completed before patient inclusion.

The novelty of this study is that it represents a change of today’s oncological practice by implementing time-based referrals to PC as opposed to and in addition to today’s ad-hoc and needs-based referral practice. The primary study objective is to investigate the effects of this complex intervention by comparing the use of chemotherapy in the last 3 months of life between the intervention and control groups. Secondary objectives focus on the use of medical interventions at the EoL, patient- and caregiver-reported outcomes, and direct costs.

### Patient-reported outcomes (PROs)

In 2006, the U.S. Food and Drug Administration (FDA) proposed the term patient-reported outcome measures (PROMs) for all measures that can best, or only, be assessed by asking the patients [30]. PROs denote an umbrella term covering the patient’s perspective on physical and psychological wellbeing, symptoms, and treatment effects [31], hence supplement clinical observations. The recognition of PROs as independent outcomes is consolidated by the Consolidated Standards of Reporting Trials (CONSORT) PRO extension statement [32] developed to improve the reporting of PROs.

Performance status and tumor burden are important predictive factors for effect of chemotherapy and survival, and closely linked to symptom burden and patient wishes. Thus, a patient-centered focus with systematic evaluation of PROs and preferences should be part of any treatment, to optimize care, particularly so as tumor-directed treatment becomes less efficient or is discontinued. Nevertheless, it is well documented that systematic symptom assessment is not routine in oncological care [33–35], although frequently used in clinical trials due to the FDA requirements [36]. Unsystematic use of PROs may in part explain inadequate symptom management. This applies to pain as well as other physical and psychological symptoms that are highly prevalent among patients with cancer, such as appetite loss, constipation, dyspnea, fatigue, anxiety, depression, and overall QoL.

Traditionally, PROs have been collected by paper forms that are perceived as cumbersome to administer, use, and store, all commonly cited barriers explaining the infrequent use of PROMs in clinical practice [33, 34]. Electronic measures, e-PROMs, can use different software and platforms, permit immediate use of real-time data in clinical consultations, and direct follow-up of patients outside hospital. E-PROMs can be programmed with a flexible and dynamic content that automatically selects the most appropriate questions to a given patient, based on a few initial screening items. They may be integrated with medical data from sources such as laboratory, imaging, and electronic health records. Studies on the use of e-PROMs in oncological care have shown that this facilitates communication [18, 37, 38], results in better patient wellbeing [27, 39], is well achieved by patients and clinicians [35], and might result in more efficient and focused consultations [40, 41]. One C-RCT demonstrated better physician satisfaction as they became aware of patient symptoms that had not been addressed [42]. A secondary analysis from a RCT with one group registering symptoms regularly suggested a potential survival benefit, but needs further investigation in larger samples [43]. Systematic electronic collection of PROs is part of PALLiON.

### Care of the caregiver

Informal caregivers frequently serve as the patient’s main source of support. In the United States, approximately 10% of about 40 million caregivers report caring for a person with cancer [44, 45]. As cancer care has shifted towards more outpatient and home-based care, the strain on caregivers is likely to increase.

Caregiving can be rewarding and positive, but the burden of caregiving might be substantial and many may not be prepared for or able to do this. Further, the caregiving experience related to advanced cancer differs from caregiving in other chronic conditions by the fluctuating, unpredictable, and often rapidly deteriorating condition of the patient. Reduced QoL and distressing symptoms such as insomnia, fatigue, anxiety, depression as well as financial difficulties are commonly experienced among caregivers [46]. Importantly, the individual caregiver vulnerability is highly associated with the perceived extent of caregiver burden [47].

One article states that early PC is an example of how to improve or maintain quality of healthcare delivery for patients and caregivers at a lower cost [48], but studies evaluating caregiver QoL, satisfaction with care, and emotional distress are equivocal. One Norwegian study [49] showed an overall positive effect on QoL, in line with studies of caregivers of patients with a poor prognosis treated by specialty-trained PC clinicians [50–52].

Two consecutive meta-analyses, covering 79 RCTs, examined the effect of different interventions on outcomes in caregivers of patients with cancer [46, 53]. The first reported small-to-medium effects on caregiver burden, coping, QoL, and self-efficacy [53], while the second concluded that caregiver interventions should be flexible and adapted to the actual situations [46]. Results from qualitative analyses indicate that provision of early PC might improve caregiver satisfaction and reduce caregiver distress [23, 54, 55]. As these interventions varied largely, no firm conclusions about which is the best approach can be drawn.

Involvement and support of caregivers are regarded key components of modern cancer care, as explicitly stated in the updated ASCO Clinical Practice Guideline on integration of PC and oncology [56]. Nevertheless, caregiver perspectives and experiences are often not adequately addressed in the consultations [47]. Hence, caregiver follow-up is systematically implemented in the PCCPs in PALLiON.

### Patient-centered care pathways (PCCPs)

Many patients perceive the healthcare system as fragmented; complaints about uncoordinated care are common [57], particularly so in transitions from one healthcare level to another [58].

The European Pathway Association (EPA) defines standardized care pathways (SCPs) as “a complex intervention of the mutual decision-making and organization of care processes for a well-defined group of patients during a well-defined period” [59]. Thus, SCPs may be a method of organizing complex care processes. In integrated oncological and patient-centered care, formalized as an SCP, healthcare professionals (HCPs) from different professions and at different locations work together to achieve common goals, i.e. better patient treatment and care. An SCP can structure individualized patient-centered care with predictable trajectories, with evidence-based diagnostics, treatment, symptom management, plus shared decision-making and family involvement. The pathway can be tailored to the individual patients in a PCCP, as in PALLiON.

The structure and content of PCCPs decide the quality of care. PCCPs may be a work plan for HCPs to optimize the use of competence and resources, i.e. providing the right competence to the right patient at the right time in the right place. Further, PCCPs may facilitate seamless transitions within and between hospitals by formalized collaboration across specialties and clarifying responsibilities. Electronic PCCPs give immediate access to useful resources such as treatment guidelines, toxicity criteria, what to address in prognostic conversations, how to promote shared decision-making, etc., all of which ensures a more uniform and quality-based interaction with the patient. A recent Lancet Commission paper proposes PCCPs as the method of choice for the integration of anticancer and patient-centered care [8], inspired by the use of PCCPs in PALLiON.

Despite the relatively consistent results from RCTs and observational studies of beneficial outcomes of early integration of PC and oncological care, it is noteworthy that designs and models of integration vary largely. Further, few studies have tested a full integration according to the criteria set forth by Leutz [60]. This indicates that there is no one right model of integration that can be implemented anywhere, and that organizational, cultural, and health policy aspects must be considered to succeed.

On this background, we have launched the national cluster-randomized, non-blinded multicenter parallel group PALLiON study, with the overall, long-term objective to integrate oncological care and PC in Norwegian cancer clinics, to improve the quality and efficacy of cancer care. PALLiON is a complex intervention containing education of physicians, implementation of PCCPs with predictable care trajectories of anticancer treatment, and patient- and caregiver-centered care with early time-based referrals to PC and systematic symptom registrations. Primary and secondary study outcomes are use of chemotherapy during the last 3 months of life and patient- and caregiver-reported outcomes.

## Methods

The trial is developed according to the Standard Protocol Items: Recommendations for Interventional trials (SPIRIT) checklist (Additional file 1).

### Design

The present study is designed as a parallel group, national, multicenter, C-RCT.

### Study objectives and endpoints

The primary study objective is to investigate the effects of the complex intervention by comparing the use of chemotherapy in the last 3 months of life between the intervention and control groups. This will be assessed using the following primary endpoint: the proportion of patients who receive chemotherapy during their last 3 months of life; and, by the first secondary outcomes, the number of cycles administered in this period, time from initiation of last cycle to death, and average time from discontinuation of last cycle to death.

Additional secondary objectives focus on: (1) the use of medical interventions / treatments at the EoL; and (2) patient- and caregiver-reported outcomes. The first will be assessed by the proportion of patients who receive this, as with the primary outcome. Patient- and caregiver-reported outcomes will be assessed every other month using well-validated questionnaires. These endpoints are defined as average area under the curve of follow-up assessments for each outcome.

Exploratory analyses will also investigate potential differences in length of survival between the two arms and examine potential differences in direct costs of care (Table 1).

**Table 1 Tab1:** Primary, secondary, and explorative objectives, and related endpoints and assessments

	Objectives	Endpoint	Assessment method
Primary	To compare use of chemotherapy in the last 3 months of life in the control and intervention groups	Proportion of patients who receive chemotherapy at EoL	Numerical and descriptive data from HCP registrations/e-CRF, last 3 months before death
Secondary	To examine the administration of chemotherapy last 3 months, medical interventions/treatments at EoL, after discontinuation of chemotherapy	Number of chemotherapy cycles, initiation, and discontinuation Proportion of patients who receive other medical interventions, i.e. concomitant medication and artificial nutrition	Numerical and descriptive data from HCP registrations/e-CRF, last 3 months of life, and after discontinuation of chemotherapy
	To compare PROs	Patient-reported symptom burden, QoL, anxiety/depression, satisfaction with information	EAPC basic dataset. EORTC-QLQ PAL15, PHQ-9, GAD-7, EORTC QLQ-INFO25
	To compare caregiver-reported outcomes	Caregiver-reported health, QoL, and satisfaction with care	SF-36, FAMCARE
Explorative	To examine length of survival	Length of survival from start of last line of chemotherapy	HCP registrations, Cause of Death Registry
	To examine direct costs	Costs of healthcare, oncology/palliative units	Length of stay, number of hospitalizations, anticancer and other medical interventions

*e-CRF* electronic case report form, *EoL* end-of-life, *HCP* healthcare provider, *PRO* patient-reported outcome, *QoL* quality of life

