### Study population

#### Inclusion criteria: participant level

##### Patients

At the second level of the C-RCT, the following eligibility criteria apply to patient inclusion:
A verified metastatic or locally advanced cancer of the upper gastrointestinal (GI) tract, lower GI tract, pancreas, liver, breast, bladder, prostate, kidney, cholangiocarcinoma, or malignant melanoma;Defined as a patient in need of PC with an anticipated life expectancy of < 12 months;Scheduled to start the anticipated last line of chemotherapy (definition: tumor directed systemic therapy). Time of inclusion that is based on the decisions about last line of chemotherapy, varies by diagnosis, and is equivalent to first line in some diagnoses;Age > 18 years;Fluency in written and oral Norwegian;Physically and cognitively able to provide written consent, based on clinical criteria, e.g. not too frail or having signs of disorientation, confusion, attention deficit, poor coordination;Scheduled to receive all oncological and specialized palliative treatment at the participating hospital, i.e. residing in the local area of the including hospital;WHO performance status 0–2.

Because gynecological and lung cancer patients receive anticancer treatment at the departments of lung and gynecology in most hospitals, these diagnoses were not included.

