**Fig. 2 Fig2:**
[figure not shown]
The chemotherapy pathway

The chemotherapy pathway as shown in Fig. 2 consists of carefully selected factors that together constitute a predictable trajectory that integrate oncological and PC for patients and caregivers.

These key factors encompass:
Clinical outcomes and PROs as these variables constitute an important premise for the decision-making regarding start, pause, or discontinuation of chemotherapy and/or other treatment strategies;Formalized, continuous collaboration between oncology and PC starting at study inclusion, with a compulsory PC consultation for all patients and caregivers;Defined responsibilities, by explicitly stating who is the primary responsible physician, the oncologist or the PC physician, depending on where the patient is in the trajectory;Systematic inclusion of patient preferences and active participation in decision-making;Involvement of family members upon start of last line of chemotherapy, and onwards;Explicit, shared, and delegated patient and caregiver responsibilities and information;Systematic symptom assessment with Eir as part of the standardized care pathway;Systematic transfer of information between the hospital, general practitioners, and the community health services;Multi-professional collaboration with referrals as needed.

All patients in the intervention arm will have regular follow-up during the disease trajectory by the PC team both within and outside of hospital, with regular assessments of PROs (symptoms, psychological distress, social support) with phone calls approximately every other week, PC consultations as needed, and assessment of need for home care or nursing home admissions.

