### The control arm

Patients in the control arm will be included when coming for start of what is the anticipated last line of chemotherapy as the same inclusion criteria apply as for patients in the intervention arm. Anticancer and other medical treatment, PC, and patient follow-up will be conducted according to established guidelines. Symptom management, contact with the hospitals’ PC teams, referral to other HCPs, care and contact with caregivers, and use of healthcare services will follow common practice. HCPs will register these activities in the e-CRFs (Table 4).

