##### Statistics

The design makes it possible to evaluate the effect of an early integration of oncology and PC at the institutional and patient levels across intervention and control arms, by comparing the use of chemotherapy in the last 3 months of life.

Analyses on the primary outcome will be performed when there are 300 patients in each arm with data on chemotherapy use in the last 3 months of life, which is the basis for the power estimation. Standard descriptive statistics will be used for background variables. Further, data will be analyzed by the intention-to-treat approach; mixed effect regression models will be used to analyze both primary and secondary endpoints in order to account for clustering. Logistic and linear regression models will be used respectively for binary and continuous outcomes and all models will be adjusted for potentially relevant baseline covariates at patient level, i.e. sex, age, diagnosis, performance status score, and baseline symptom scores. The analysis of the main outcome will also be adjusted by size of the catchment areas, which is the randomization stratification factor.

Survival analysis methods, i.e. Kaplan–Meier curves and Cox proportional hazards models with shared frailty terms to account for clustering and Kaplan–Meier curves, will be employed in order to model time to death. Sensitivity analyses to different methods will be applied to handle missing data in the secondary PROs: complete case analysis and multiple imputations. This also applies to patient- and caregiver-reported outcomes. Paper forms will be used to collect medical data and PROs for comparisons across arms.

Further, a potential effect of the intervention at each of the centers in the intervention arm may be evaluated at a later stage as an explorative outcome by comparing post-intervention data with historical data, e.g. on use of chemotherapy and number of readmissions/emergency admissions in the very last stages of life as appropriate.

The CONSORT recommendations for reporting RCTs will be followed. The CONSORT recommendations for reporting C-RCTs will be followed. IBM SPSS Statistics for Windows, version 25.0 (IBM Corp., Armonk, NY, USA) and STATA (Stata Corp. LCC, College Station, TX, USA) will be used.

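### Exploratory survival is counted from start of the last chemotherapy line instead of from inclusion, so an included patient who never starts has no time origin

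*Protocol article*

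**What the plan says.** Under Study objectives and endpoints, the article announces: "Exploratory analyses will also investigate potential differences in length of survival between the two arms". The explorative row of Table 1 gives the endpoint as "Length of survival from start of last line of chemotherapy".

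The participant-level inclusion criteria require that the patient is "Scheduled to start the anticipated last line of chemotherapy". The Abstract (Methods) says that patients and caregivers "are included when patients come for start of last line of chemotherapy". The control arm section agrees: "Patients in the control arm will be included when coming for start of what is the anticipated last line of chemotherapy".

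The section on the patient-centered care pathways describes oncology and palliative care collaboration "starting at study inclusion, with a compulsory PC consultation for all patients and caregivers". It also says that the clinical and patient-reported variables in the pathway inform decisions on beginning, interrupting or ending chemotherapy.

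The Statistics section states that "data will be analyzed by the intention-to-treat approach". It names Kaplan–Meier curves and Cox models with shared frailty for time to death, but gives no time origin of its own. Table 1 is therefore the only place where the origin is fixed.

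**The concern.** A between-arm survival comparison needs a time zero that every included patient has and that the intervention cannot move. Start of chemotherapy need not meet either condition. Eligibility rests on being scheduled to start, so someone can be included and then deteriorate, decline or die before the first dose. In the intervention arm, the pathway that bears on the decision to start is already running.

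Two things follow from the literal wording. First, non-starters have no origin and drop out of an analysis that is said to be intention-to-treat. If they are the frailer patients and are more numerous in the intervention arm, survival there looks longer than it is. Second, the line is only anticipated to be the last. If another line follows, it is unclear whether the clock starts at the line that led to inclusion or at the one that proved to be last.

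**Working it through.** **Plan figures.** The article states no sample size, event count or power for survival, so there is no survival figure to reproduce. The only count used here is 340 enrolled per arm. It agrees with the plan's 300 per arm and 12% attrition: 300 / (1 − 0.12) = 340.9.

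**Order of events.** The eligibility wording puts inclusion before the first dose. The Abstract and the control arm section put it at the visit for start of the line. Together they imply a short gap, but not a gap of zero for every patient.

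**Illustration of non-start.** All inputs are assumptions, because the documents give none:

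- no true effect, and median survival 8 months from inclusion;
- patient hazards vary with a gamma frailty (shape 2, mean 1);
- non-starters are the patients with the highest frailty, measured with some random error;
- censoring at 12 months;
- measure: rate ratio = (deaths / person-time, intervention starters) / (deaths / person-time, control starters).

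Patients lost = 340 × control share + 340 × intervention share, each rounded.

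| Non-start, control vs intervention | Patients lost of 680 | Median among starters, months | Rate ratio |
|---|---|---|---|
| 0% vs 2% | 0 + 7 = 7 | 8.00 vs 8.20 | 0.98 |
| 2% vs 5% | 7 + 17 = 24 | 8.21 vs 8.48 | 0.97 |
| 2% vs 10% | 7 + 34 = 41 | 8.20 vs 8.93 | 0.93 |
| 5% vs 15% | 17 + 51 = 68 | 8.47 vs 9.37 | 0.92 |

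With the origin at inclusion, all 680 patients contribute and the ratio is 1.00 under the same assumptions.

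**Illustration of delay.** For a patient who starts in any case, a later start shortens measured survival by the extra delay. With 0.25 month in control, an intervention delay of 0.5 month costs 0.50 − 0.25 = 0.25 month, and a delay of 1 month costs 1.00 − 0.25 = 0.75 month. This component makes the intervention arm look worse.

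A longer gap also lets more patients die before starting, and these are again the frailer ones. Under the assumed frailty model S(t) = (1 + ct)^−2. A median of 8 gives c = (√2 − 1)/8 = 0.0518. The share dead before start is 1 − S(d): 2.5% at d = 0.25, 5.0% at d = 0.5 and 9.6% at d = 1. Median survival from start among those who do start is 8 + (√2 − 1)d, that is 8.10, 8.21 and 8.41 months.

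With those early deaths dropped, the simulated rate ratio is 0.99 for 0.25 vs 0.5 month and 0.97 for 0.25 vs 1 month. In this model the loss of early deaths slightly outweighs the shortened clock. With a constant hazard the two would cancel, because remaining survival would not depend on the delay. Delay alone is thus a matter of 1–3% here, and its net sign depends on the assumed hazard.

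**The case against.** The best defence is that the Table 1 phrase is shorthand for inclusion. The Abstract and the control arm section use nearly the same words for the moment of inclusion. On that reading nobody is dropped and the analysis is intention-to-treat as stated. This stands as an account of what was probably meant, and it is why the effect is probably small. It does not remove the problem in the wording, since eligibility asks only for a scheduled start and the one stated origin is a treatment event.

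Four stronger readings are tempting, and the documents do not support them.

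- A reader might infer that the survival analysis is not intention-to-treat. It departs from that principle only as far as included patients fail to start and are then left out. No section reports non-starters or says that they are excluded.
- A reader might infer that the intervention delays or prevents starts. The pathway informs that decision, but the four sub-pathways begin with chemotherapy, and the order of palliative consultation and first dose cannot be read from the text.
- A reader might infer that only intervention patients fail to start. Control patients can also deteriorate, decline or die first.
- A reader might put the spurious hazard ratio as low as 0.86. That needs 15% of patients with a median survival of 2 months, all of them not starting in the intervention arm and none failing to start in control. It sits badly with eligibility limited to performance status 0–2 and patients not too frail to consent.

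It is also fair to say that the article's remarks on a survival benefit of early palliative care describe earlier literature. For this trial, survival is only explored.

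**Conclusion.** The point holds as a wording fault with a small possible bias. Table 1 fixes a time origin that can follow inclusion, that some included patients may never reach, and that is ambiguous if a further line is given. Taken literally, this conflicts with the intention-to-treat statement.

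Under assumed non-start of 0–5% in control and 2–15% in the intervention arm, a null rate ratio moves to about 0.98–0.92, an apparent 2–8% lower death rate. That range and its direction rest on two assumptions: frailer patients are the ones who do not start, and non-start is more common in the intervention arm. The shortened clock of late starters pulls the other way, and the net effect of delay is minor. If inclusion and start nearly always coincide, the bias is close to zero.

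The endpoint is exploratory, and no primary or secondary conclusion depends on it. This is a minor, free improvement.

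**What to change.** State in Table 1 and in the Statistics section that survival is counted from the date of inclusion (consent) for all included patients in both arms. If time from start of chemotherapy is of interest, report it as a descriptive supplement, naming the line that led to inclusion as the one meant and giving the number of non-starters in each arm.

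The cost is one clause in two places. Date of consent is already on the baseline patient form, so no new data are needed.

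One limit should be stated. Hospitals were randomized before patients were included, so inclusion itself comes after randomization. The change keeps every included patient in the comparison, but it does not remove any difference between arms in who was recruited.
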